### Objectives {7}

The central hypothesis of our program is that the proposed assistive wearable will support spatial cognition and more efficient navigation, augmenting personal freedom and agency, and promoting health and well-being in people with BLV. In order to achieve this goal, we will complete the following objectives:Digital twin (map) a campus in Thailand to enable accurate and precise localization for students on campus**.** Therefore, a more efficient navigation support service will be created and foster optimal wayfinding. We will test mobility and anticipate greater activity and a wider home range (more land coverage)**,** and shorter traversal times for given initial/intended map-points.Test acceptability, appropriateness, and feasibility of our approach. We will adapt VIS^4^ION based on the input from this formative testing.Perform an extended-use randomized controlled trial with VIS^4^ION.Test a wider coverage area, assessing generalizability. We intend to connect our campus of interest to urban Bangkok.

### Trial design {8}

#### Phase 1

Aim 1: Create a “digital twin” of a particular campus (Ratchasuda — a disability college), testing both the performance of the service itself as well as the functional impact of the system.

Aim 2: Assess the ecology of VI students using the wearable, assessing the home range and activity level. A cohort of 20 VI students will use the wearable during navigation (1 week) in two phases: an initial passive phase, during which the wearable will only record location, and then an active phase, during which the location recording will be enhanced with orientation cueing.

Aim 3: Assess the acceptability, appropriateness, and feasibility of the wearable, as a navigation aid for the BLV, using the results of interviews and surveys to implement improvements to the system.

#### Phase 2

Aim 4: We designed an exploratory experiment to assess and monitor our participant’s health-related changes (increased mobility and QoL). This phase is planned as a prospective, randomized crossover, controlled, non-blinded study to compare to evaluate the effectiveness of the wearable for increasing navigation and quality of life. Twenty BLV participants will be randomized to group A (10 participants) and group B (10 participants). During the first 15 days, group A will go through an active phase and then a passive phase for the next 15 days. Reciprocally, group B will go through a passive phase for the first 15 days and then an active phase for the second half of the month.

Aim 5: We will test the generalizability of the new mapping service in a more challenging environment — testing system performance in Bangkok.

## Methods: participants, interventions, and outcomes

### Study setting {9}

Our study will be performed at Mahidol University in Thailand. Areas like this small town in Thailand lack sophisticated technologies and facilities and are therefore an important test case for evaluating a new technology that is intended to be used worldwide for BLV individuals in both low- and higher-income areas and countries.

To provide inclusive higher education for all and equal access to learning and socially engaging activities, Ratchasuda College at Salaya (the largest campus of Mahidol University) provides short course trainings on orientation and mobility, accessible information access for the blind, as well as master-level degree programs focused on blind rehabilitation.

As Ratchasuda College is aware of the bottlenecks in the education and employment of BLV students, pre-college activities have been created with eleven blind schools located throughout Thailand. Transition management and disability support services are mechanisms to facilitate progression to higher levels of education and employment. We aim to expand our scope using this network and these mechanisms; we also plan to leverage collaborations with institutions in the provinces of Khon Kaen and Songkla.

### Eligibility criteria {10}

Inclusion criteria (patients with visual impairment).

Participants with visual impairments will meet the following criteria:Older than 18 years,Medically diagnosed with visual impairment (legal blindness — as per the US government standards and the Social Security Administration, including acuity and/or field deficits)Currently using a primary assistive device for mobility (e.g., white cane or guide dog)Able to travel independently (without aid of another person)

Exclusion criteria include:Significant injury to the upper and/or lower extremity,Comorbid neurological illness,Confounding medical conditionsPregnancyAuditory impairmentsSomatosensory impairments to the trunk or torso that precludes the use of the haptic interfaces

### Who will take informed consent? {26a}

The consent process will take place in a private room by an IRB-approved study staff member. Once an appointment is scheduled with a participant who verbally expresses an interest in the study, a trained member of the research team will verbally explain the purpose of the study to the participants, the potential benefits and risks (minimal in this case) they may experience, and the voluntary nature of their participation. The language that will be used regarding the explanation of the study and participation consent will be no higher than a 6th grade language level and it will be in a language understandable to the subject (English\Thai). Written informed consent will be obtained when participants agree to participate, and they are able to explain their understanding of the study to the trained research team members. If they cannot, the research team member will review the study with them again, if they still cannot explain the study back, they will not be enrolled. A copy of the consent agreement will be provided to participants for reference. Any questions will also be answered at this time. All efforts will be made to make the consent process free of coercion.

### Additional consent provisions for collection and use of participant data and biological specimens {26b}

Not applicable, we will not collect and use participant data and biological specimens for ancillary studies.

### Intervention description {11a}

#### Aim 1

Two study members will carry a specialized wearable for mapping with 3 extra stereoscopic camera units and physically ambulate the entire MU-RC campus, as pictured in Fig. 2. This data acquisition phase will be completed in a series of five 2-h blocks, as determined by a prior feasibility analysis. Each study member will complete two data acquisition recording series (i.e., 10 blocks). The mapping data will be compared intra-recorder (between series) and inter-recorder and then barring fidelity issues will be used for the pipeline, as delineated in the overview section. Each block will be pre-defined and reviewed with the study team member, at outset, and again on each recording day, and all data will be checked for validity. Following data acquisition and the mapping sequence (reconstructions), localization queries will be performed across RC (50 in total, evenly spread across campus) and compared to ground truth. We have defined parameters for city blocks covered/pedestrian hour of mapping and storage estimates for data acquired.

**Fig. 2 Fig2:**
[figure not shown]
Aerial map of Ratchasuda College (RC) at Mahidol University. A route between two on-campus locations is delineated

#### Aim 2

We will recruit a cohort of twenty BLV students currently enrolled in classes at Mahidol University. Students will be asked to don a wearable (bookbag) during all tasks requiring navigation for one week (10 days)**.** Ethograms will be constructed by coding the basic behaviors documented while navigating particular sections of campus, including public transport access points, street crossings, street hazards, e.g., areas with scaffolding, navigation to and through entrances, straight paths (to assess veering), curved paths, and elevation changes, e.g., stairs and ramps. We will collect data on the behavioral components of each situation to understand the effects of the environment on the participant as one moves through campus and the variables that trigger and modify related behaviors [27]. We will describe the mobility phenotype as BLV users interact with a complex range of obstacles in the various areas of campus, cataloging the vastly different reactions and consequences triggered by each. Particular obstacles and campus areas may have a higher likelihood of precipitating mechanical falls, leading to potentially catastrophic injuries. Thus, this process will guide the training of machine learning algorithms based on the specific task to be completed. For example, an intersection crossing near a bus stop for someone with a high degree of veering is particularly precarious; this and other related findings require specific attention and additional safety prompting. We will test navigation assistance (short-term) by comparing the initial five days with the VIS^4^ION system worn in passive mode (acquiring data, providing no assistance/feedback on location and orientation) to the final 5 days with the system worn in active or assistive mode (acquiring data and simultaneously providing assistance/audio feedback).

#### Aim 3

We will ask the same cohort of BLV students enrolled in Aim 2 to participate in focus group discussions (FGD) to assess the acceptability and appropriateness of VIS^4^ION. A research team member will conduct FGDs, each of which will consist of 6**–**8 individuals, and an interpreter will help facilitate the discussion [28].

Each FGD session will last roughly 60 min and include participants’ perceptions and experiences while navigating the VIS^4^ION system. The FGDs will be guided by pre-determined questions related to general perceptions of the VIS^4^ION system, as well as thoughts on the facilitators and barriers of the intervention. The FGD sessions will be audio-recorded verbatim and later transcribed and translated into English by the research team. During the sessions, the research team member will also take field notes.

#### Aim 4

A cohort of 20 (new) participants will be recruited to assess extended-use benefits over one month. We will create two groups for the randomized crossover design. Each participant will be randomized to either sequence A (10 participants) or sequence B (10 participants). During the first 15 days, group A will go through an active phase and then a passive phase for the next 15 days. Reciprocally, group B will go through a passive phase for the first 15 days and then an active phase for the second half of the month. During the passive phase, the wearable will be maintained in a monitoring mode and simply acquire data, providing no assistance/feedback on location and orientation. During the active phase, the wearable will have an activated assistive mode, i.e., the wearable will acquire data and simultaneously provide assistance/audio feedback. We will evaluate the effectiveness of the wearable for increasing navigation and quality of life. We hypothesize that the VIS^4^ION wearable will improve navigation and quality of life in individuals with visual disabilities.

During the active phase, subjects will complete their daily activities while wearing VIS^4^ION and using the mapping and localization microservice to facilitate wayfinding. Throughout the study we will monitor navigation performance through the same metrics as delineated in Aim 2 [week 2 compared to week 4], as well as to monitor for any falls that may occur (IMU-based alerting); we will also subjectively assess visual function through the 25-Item National Eye Institute Visual Function Questionnaire (VFQ25) [29], physical function and mobility, through the International Physical Activity Questionnaire (IPAQ) [30, 31], and QoL, through the World Health Organization QoL Brief (WHO-QoL-BREF) [32, 33]. The subjective assessments will be performed on day 0 (day of device delivery and initiation) and on the final day of the trial (day 31).

We will also use the Saunders Framework [34] to conduct a process evaluation of the intervention. This process evaluation will monitor program implementation to better understand the relationship between intervention components, process/implementation measures, and health outcomes. The Saunders Framework provides a systematic approach for assessing key process measures across several domains. This approach will generate both formative and summative data [35–37]. A combination of quantitative and qualitative approaches will be utilized, including observation forms, checklists, surveys, record review, FGDs, and KIIs (key informant interviews). Study participants, clinical staff, and study and clinical encounter forms will be the sources of data. Members of the research team will conduct semi-structured interviews with students’ post-experiment; the session will be audio-recorded verbatim. Interview audio-recordings will be transcribed and translated into English by the research team. Special emphasis will be placed on Thai cultural and lifestyle preferences.

#### Aim 5

We will recruit a cohort of twenty BLV students to assess the generalizability of our previously described techniques. We will extend our mapping/localization program from the RC campus to a 12-block portion of Bangkok (Fig. 3), giving students the opportunity to more easily access the vibrant city center. To address the challenge of image-based mapping/localization in a large-scale environment, we will divide the large-scale territory to be mapped into smaller territories, roughly breaking down the proposed area of study into one block region. We intend to add a coarse localization tool, using GPS and the embedded IMU in the camera, to efficiently narrow down our search space from the entire territory to a smaller regional city block, subsequently we can deploy our image-based techniques.

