**Methods:**

We are leveraging 3D reconstruction and semantic segmentation techniques to create a digital twin of the campus that houses Mahidol University’s disability college. We will do cross-over randomization, and two groups of randomized VI students will deploy this augmented platform in two phases: a passive phase, during which the wearable will only record location, and an active phase, in which end users receive orientation cueing during location recording. A group will perform the active phase first, then the passive, and the other group will experiment reciprocally. We will assess for acceptability, appropriateness, and feasibility, focusing on experiences with VIS^4^ION. In addition, we will test another cohort of students for navigational, health, and well-being improvements, comparing weeks 1 to 4. We will also conduct a process evaluation according to the Saunders Framework. Finally, we will extend our computer vision and digital twinning technique to a 12-block spatial grid in Bangkok, providing aid in a more complex environment.

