## Assignment of interventions: allocation

### Sequence generation {16a}

During the study’s second phase, a block randomization will be conducted, assigning participants to either group A or group B. When participants agree to participate, a number will be randomly assigned to them using Excel random number generator. Then, two randomization lists will be created using Excel random number generator, creating separate lists for group A and group B.

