**Fig. 4 Fig4:**
[figure not shown]
Correlations between ground truth positions and those computed from Pos-Net and Loc-Net (left) and corresponding 2D errors (right)

We have collected a small sample of preliminary data (Fig. 4) to demonstrate the feasibility of these analyses, and that they are capable of demonstrating improvement (green; Loc-Net) relative to our baseline (blue; prior art) methods. There is a clear, qualitative improvement in the green plots, both in precision (left, improved correlation) and accuracy (right, error scatter). Our ability to discriminate between methods will only improve with the larger dataset proposed for this aim.

#### Aim 2

We will use the trained network to predict the real-time pose of a BLV user and create a mobility home range for each participant during both the passive and active phases of this initial pilot. We anticipate that route planning will improve through more efficient wayfinding in the active phase, when users have a more comprehensive understanding of the local environment (spatial cognition). We will extract paths between pre-selected pairs of locations during the active and passive phases (e.g., residence to classroom building) traversed in the pre (first 5 days) and post (last 5 days) periods to evaluate our predictions, measuring:Average changes and variability in path length (i.e., percent change in path length [difference test based on binomial distribution] and path variance [F-test of variances])Average changes in normalized traversal time (i.e., percent change in time [difference test based on binomial)For destinations that denote social activities, estimate the difference in time spent on such activities pre to post [time difference based on Wilcoxon signed rank test].Pre vs. post fall rates using an exponential waiting-time model of time between falls [Poisson rate of falling]Total area covered on an hourly, daily, and weekly basis to assess a home range

#### Aim 3

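### Aim 2's fixed passive-then-active order confounds device mode with practice, so it cannot demonstrate improved travel; Aim 4 carries a secondary, conditional carryover caution

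*Protocol article*

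**What the plan says.** **Aim 2.** Trial design {8} describes "an initial passive phase, during which the wearable will only record location, and then an active phase". Intervention description {11a} says "We will test navigation assistance (short-term) by comparing the initial five days" in passive mode with the final five in active mode. Statistical methods {20a} takes paths between pre-selected pairs of locations, "traversed in the pre (first 5 days) and post (last 5 days) periods to evaluate our predictions". Randomisation is confined to the later part of the programme: "During the study’s second phase, a block randomization will be conducted, assigning participants to either group A or group B" (Sequence generation {16a}). The Sample size section holds the article's only power calculation. It concerns path length in the first phase, with 20 subjects, and states its purpose as showing that travel has improved.

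**Aim 4.** The crossover runs 15 + 15 days: "During the first 15 days, group A will go through an active phase and then a passive phase for the next 15 days", while "group B will go through a passive phase for the first 15 days and then an active phase". The closing questionnaires are on day 31, and navigation is compared between week 2 and week 4. Trial design {8} calls this aim exploratory.

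**Mechanism.** For Aim 2 the article expects better route planning in the active phase, "when users have a more comprehensive understanding of the local environment (spatial cognition").

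**Abstract.** "A group will perform the active phase first, then the passive, and the other group will experiment reciprocally". The next sentence places the acceptability assessment with these participants, and a different cohort is then described for health and well-being. In the body, acceptability is assessed in the Aim 2 cohort, whose order is fixed.

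**The concern.** With one sequence, mode and period are the same variable. Anything that changes between the first and second five days enters the estimated device effect in full: getting used to the backpack, walking the same routes again, being watched, calendar effects. A device with no effect could yield a significant change, which would then be read as evidence of benefit. A reader of the abstract alone could also believe that the order in this cohort had been randomised.

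Aim 4 randomises the order, so practice common to both groups cancels. The remaining worry is learning specific to the active phase. If cueing teaches group A the routes, its later passive phase is no longer a clean control, and a real effect would be understated.

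**Working it through.** **Inputs from the protocol article.** n = 20; path-length ratio 0.6, so |ln 0.6| = 0.511; SD of length-ratios 2.5 (Sample size). Aim 4 allocation 10:10, periods 15 + 15 days.

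**Assumed, because not stated.** Alpha 0.05. The SD of 2.5 is read as a ratio, so the log SD is ln 2.5 = 0.916. The practice effect, the retained fraction c and the intraclass correlation are also assumed.

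**Plan's own figure.** The standard error is 0.916/√20 = 0.205, and 0.511/0.205 = 2.49. A one-sided normal test gives Φ(2.49 − 1.645) = 0.80, which reproduces the stated power. Two-sided, the normal test gives 0.70 and the t-test 0.66. This calculation treats the whole passive-to-active change as the device effect.

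**Aim 2.** The expected estimate is the device effect plus the period effect. With the device effect at zero, the noncentrality is |ln(1 − q)|/0.205 for a practice change of q. Two-sided paired t, 19 df:

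| Practice change q | abs. ln(1 − q) | Noncentrality | P(significant) |
|---|---|---|---|
| 10% | 0.105 | 0.51 | 0.08 |
| 20% | 0.223 | 1.09 | 0.18 |

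The nominal rate is 0.05. A smaller SD would raise these probabilities, but the documents give no basis for one. The article names a binomial-based difference test for path length and time, so the t-test is a stand-in.

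**Direction.** For traversal time, practice shortens it and Objectives {7} predicts shorter times, so the bias favours the device. For path length, the Sample size section has initial paths 40% shorter than aided ones, whereas Objectives {7} and Statistical methods {20a} expect more efficient navigation. On the first reading, practice that shortens paths works against the powered hypothesis: a one-sided 0.05 t-test in that direction is significant in under 0.5% of trials at q = 20%. On the second reading it works for it.

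**Aim 4.** Let τ be the device effect, π a common period effect and c the fraction of τ retained in group A's passive phase.

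- Group A, active minus passive: τ − (π + cτ)
- Group B, active minus passive: π + τ
- Mean of the two: τ(1 − c/2)

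The period effect cancels and the carryover does not. With τ = ln 0.6:

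| c | Share of τ estimated | Apparent reduction |
|---|---|---|
| 0 | 100% | 40.0% |
| 0.25 | 87.5% | 36.0% |
| 0.5 | 75% | 31.8% |
| 1 | 50% | 22.5% |

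**First-period contrast, 10 v 10.** The between-person SD follows from the log-difference SD and the intraclass correlation: √(0.916²/[2(1 − ICC)]), which is 0.916 at ICC 0.5 and 1.183 at 0.7. Noncentrality is 0.511/(SD × √0.2) = 1.25 and 0.97, so two-sided power on 18 df is about 0.22 and 0.15.

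**The case against.** - **Aim 2 is called an initial pilot and a randomised aim follows.** True, but the Sample size section still gives it a demonstrative purpose and Statistical methods {20a} attaches inferential tests. The label does not cover that use.
- **Practice may be small.** The students are already enrolled on the campus, travel independently and would walk habitual routes such as residence to classroom. This stands. It limits the likely size, and it also limits how much new route knowledge could carry over in Aim 4. The backpack and the observation would still be new.
- **The direction is not settled for path length.** This also stands, as shown above. A reader might infer that Aim 2 will overstate the benefit on path length and that the two aims are biased in opposite directions. The documents support that only for traversal time.
- **Aim 4 is exploratory and no power is claimed for it.** A reader might infer that it will certainly underestimate the effect. The article speaks of better understanding during the active phase and does not say that it persists. Comparing week 2 with week 4 also leaves days 16 to 21, about six days, between the switch and the second measurement. That may absorb transient effects, though not routes once learned.
- **A statistical analysis plan may add a first-period or carryover analysis.** Its absence from the article is therefore no fault. For Aim 2 that defence is not available, because no model can separate order from mode in one sequence.

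**Conclusion.** The confounding in Aim 2 is a fact of the stated design and needs no assumption. The passive-to-active change cannot by itself support a claim that the device improved travel.

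Its size cannot be derived from the documents. The 8% and 18% figures are hypothetical: they rest on assumed practice effects of 10% and 20%, on reading the SD as ln 2.5 and on a two-sided paired t-test at 0.05. They do not predict the trial's error rate.

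For Aim 4 the finding is a conditional caution. If a fraction c of the effect is retained, the active-minus-passive estimate falls to (1 − c/2) of the truth, toward zero. Whether c exceeds zero is unknown.

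The abstract's placement of the randomised design conflicts with the body and is a wording error to correct.

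**What to change.** **Aim 2, simplest option.** Report the passive-to-active change as a descriptive pilot result, remove the statement that it demonstrates improved travel, and rest the comparative claim on the randomised Aim 4, worded to fit that aim's exploratory status. The cost is wording and a weaker claim from the first cohort.

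**Aim 2, alternative before enrolment.** Randomise the 20 students 10:10 to passive-first or active-first and analyse mode with a period term. Trial status says enrolment had not begun. The costs are a randomisation list, possible carryover in active-first students, and no prior passive baseline for them. The last matters if the baseline collision rate in Interim analyses {21b} comes from the passive phase, which the article does not say.

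**Path length.** Reconcile the direction in Sample size with Objectives {7} and Statistical methods {20a}.

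**Aim 4.** State that the crossover estimate is diluted if route knowledge is retained. Show the first-period 10 v 10 contrast only as a sensitivity analysis, noting its power of about 0.15 to 0.22 under the assumptions above. The cost is one sentence and one extra analysis.

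**Abstract.** Attach the randomised two-order design to the Aim 4 cohort and describe the acceptability cohort as fixed-order, unless the Aim 2 order is randomised.
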